**3.4 Intervention**

The intervention will take place from 05/01 to 08/30/2019.

Participants will measure their capillary blood glucose before leaving home and, if their blood glucose level is lower than 80 mg/dL or higher than 200 mg/dL, they will not participate in the intervention on that day, and another date will be scheduled. Subjects must arrive at the place where the intervention will take place (at the UPA of Núcleo Bandeirante) between 7:00 am and 8:30 am, and fasting for 8 to 11 hours. In the night before, everyone will eat two standard meals (dinner and supper).

In random order, they will be instructed to consume the standard breakfast, or a standard breakfast plus one of the test foods (foods that will be tested: 3 g of cinnamon powder; 3 g of cinnamon in capsules; 6 g of cinnamon powder; 6 g of cinnamon in capsules; 100 g of lettuce; 100 g of tomato; 30 ml of extra virgin olive oil; 115 g of mixed salad containing 50 g of lettuce, 50 g of tomato and 15 ml of extra virgin olive oil; 150 g of avocado; 15 g of wheat bran; 15 g of chia seeds or 15 g of golden flaxseed flour), within 15 minutes. After consuming each meal, participants will complete the Visual Analogue Scale (**ANNEX II**) to assess palatability, considering appearance, smell, texture, flavor and intensity of flavors (sweet, salty, bitter and sour) (Flint *et al.* , 2000). The glycemic curve will be monitored for 120 minutes at times 0, 15, 30, 45, 60, 90 and 120 minutes. Capillary blood glucose determination will be carried out using the Accu-Check Active device (Roche Diagnostics) made available by the researcher and will be the option of choice so that glycemic results are known quickly and the patient is not exposed to the risk of unmonitored hypoglycemia. The positive area formed below the glycemic response curve will be calculated using the trapezoidal method. Washout application will be for a minimum of 3 days and a maximum of 10 days.

Table 1 presents the nutritional information of the standard breakfast that will be offered to patients. The nutritional value corresponds to approximately 15% of the total energy value of a standard diet of 2,000 kcal, containing 59.4% carbohydrates, 28.6% lipids and 12.0% proteins and is in accordance with the Brazilian Diabetes Society Guidelines (2017).

Table 1. Nutritional information for the standard breakfast

| **Food** | **Quantity** | **CHO (g)** | **LIP (g)** | **PTN (g)** | **Fibers (g)** | **Lime** |
| --- | --- | --- | --- | --- | --- | --- |
| Fruit juice | 200ml | 22.00 | 0.00 | 0.00 | 0.90 | 88.00 |
| Savory toast | 40g | 26.67 | 3.20 | 5.47 | 1.47 | 157.36 |
| Processed cheese | 20g | 0.67 | 5.13 | 2.00 | 0.00 | 56.85 |
| *Light* processed cheese | 20g | 0.67 | 2.40 | 2.60 | 0.00 | 34.68 |
| **Total** |  | **50.01** | **10.73** | **10.07** | **2.37** | **336.89** |

Quantity: quantity; CHO: carbohydrates; LIP: lipids; PTN: proteins; Cal: calories.

Source: Food label.

The standard meal plus the foods to be tested will have similar amounts of carbohydrates and proteins (nutrients capable of increasing blood glucose). Patients with diabetes will have cinnamon powder or wheat bran or chia seed or flaxseed flour added to their breakfast juice. In two experiments, cinnamon will be offered in capsules and must be ingested with the juice. Lettuce or tomato or olive oil or mixed salad or avocado will be offered with breakfast and must be consumed within the 15-minute time limit. The products will be divided on a high-precision scale. Individuals will be instructed to chew slowly and the time for ingestion will be monitored and cannot exceed 15 minutes with the aim of promoting the absorption of substrates in a similar way among individuals.

The choice of foods was made by reviewing data in the literature on foods with potential hypoglycemic effects and the portion sizes were adopted considering the low amount of carbohydrate available (which corresponds to total carbohydrate minus the amount of fiber) and proteins, which are the nutrients capable of promoting glycemic elevation. The researcher ate all the meals to be tested to assess the presence of problems related to swallowing the combined foods and portions adopted, and there were no complications. Table 2 contains the nutritional information for the foods tested.

**Table 2.** Nutritional information of the products that will be tested

| Test foods | Quantity | Energy  (Lime) | Carbs  Total (g) | Fat  Total (g) | G. Poli  (g) | G. Mono  (g) | G. Sat  (g) | Protein  (g) | Fiber  Total (g) | Fiber  Soluble (g) | Fiber  Insoluble (g) |
| --- | --- | --- | --- | --- | --- | --- | --- | --- | --- | --- | --- |
| Cinnamon powder | 3g | 10.92 | 2.39 | 0.10 | 0.02 | 0.01 | 0.02 | 0.12 | 1.63 | na | na |
| Cinnamon powder | 6g | 21.84 | 4.79 | 0.19 | 0.03 | 0.03 | 0.04 | 0.24 | 3.26 | na | na |
| Lettuce | 100g | 7.64 | 1.5 | 0.11 | 0.06 | tr | 0.15 | 0.41 | 1.25 | 0.6 | 0.65 |
| Tomato | 100g | 19.44 | 3.82 | 0.17 | 0.08 | 0.03 | 0.03 | 1.04 | 1.03 | 0.25 | 0.78 |
| Olive oil | 30ml | 270 | 0.00 | 30.00 | 2.85 | 22.65 | 4.47 | 0.00 | 0.00 | 0.00 | 0.00 |
| Lettuce (50g), tomato (50g) and Olive Oil (15ml) | 115g | 149.8 | 2.66 | 15.14 | 1,495 | 11.34 | 2,325 | 0.725 | 1.14 | 0.425 | 0.715 |
| Avocado | 150g | 125.84 | 8,775 | 9,315 | 1.56 | 4.77 | 2.55 | 1,725 | 6,045 | 2,505 | 3.54 |
| Wheat bran | 15g | 53.81 | 9,675 | 0.639 | 0.3315 | 0.096 | 0.0945 | 2.34 | 6,285 | 0.465 | 5.82 |
| chia seed | 15g | 84.35 | 6.3 | 5.1585 | 4.0995 | 0.555 | 0.5025 | 3.18 | 6.18 | 0.795 | 5,385 |
| Golden flaxseed flour | 15g | 76.8 | 4.5 | 5.2005 | 3.9 | 0.9 | 0.4005 | 3 | 3.9 | 1.2 | 2.7 |

Quantity: quantity; Cal: calories; CHO: carbohydrates; G. Poly: polyunsaturated fats ; G. Mono: monounsaturated fats; G. Sat: saturated fats; tr : dashes.

**Source:** [Philippi , ST.](https://www.sciencedirect.com/science/article/pii/S2211335518300688#bbb0180) Food composition table: support for nutritional decision-making . Editora Manole, Barueri, 2013.

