**3 . MATERIAL AND METHODS**

**3.1 Experimental design:** the research is designed as a *crossover clinical trial* .

3.2 Description and selection of the population and sample: 22 subjects with type 2 diabetes treated at the Health Centers of Núcleo Bandeirante, Riacho Fundo I or Candangolândia will participate in this study. They will be invited to participate by putting up posters and giving lectures to publicize the study that will take place at the UPA of Núcleo Bandeirante. The sample size was defined considering the results of the study of De Carvalho *et al.* (‎2017) and the calculation was made by the *G Power* program version 3.1.9.2 (University of Düsseldorf, Germany), which indicated the need for at least 19 participants in each experimental group, to which we added 15% to compensate for possible losses. A significance level of 5% was adopted.

The inclusion criteria will be: to have a diagnosis of type 2 diabetes (American Diabetes Association , 2017); age between 30 ≥ and < 60 years; to consume breakfast regularly (≥ 100 kcal ingested, within 2 hours after waking up, on ≥ 4 days of the week); to be not allergic to the foods tested/used in the study; to agree to eat all study foods; to report no sleep disorders or use sleeping medication; to have availability of time to participate in all meetings within a period of up to 3 months and to agree to participate in the research by signing the Free and Informed Consent Form (TCLE).

Subjects that will be excluded from the study are those who: use exogenous insulin or medications for pathologies other than DM2; have complications from diabetes; smoke; have gastrointestinal disorders or irregular intestinal rhythm; have psychiatric disorders with impaired understanding; participate in other research protocols; refuse to provide or are not able to provide relevant data to the research and who do not attend previously scheduled tests for three times after confirming their presence in the day before the intervention.

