3.3 Initial interview

Volunteers will participate in an initial interview to collect the following data: age, education, anthropometry, smoking, time since diabetes diagnosis, use, type and dosage of medications, presence of allergy and/or food intolerance, intestinal function, number of hours of sleep and self-reported sleep quality, breakfast and fiber consumption habits (**ANNEX I**).

Body weight will be determined using a digital electronic scale and height will be measured using a vertical anthropometer. The body mass index (BMI) value will be calculated and classified according to the recommendations of the World Health Organization (WHO, 2003) . Waist circumference will be measured by determining the midpoint between the lowest rib and the iliac crest, with a flexible and inelastic measuring tape (Heyward & Stolarczyk, 2000). Participants will also undergo body composition assessment using the double emission X-ray densitometry (DEXA) method before and after the end of the intervention.

Volunteers will be instructed to follow individualized nutritional prescriptions, to abstain from alcohol and physical exercise in the 24 hours prior to participating in the research.

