**3.5 Statistical Analysis:**

Sample characterization data and meal palatability will be analyzed using the mean ± standard deviation. To compare the average palatability scores, the Shapiro- Wilk test will be applied.

To examine the effects of the tested meals and time on blood glucose, two-way analysis of variance (ANOVA) with repeated measures will be performed with *post hoc* comparisons using the Bonferroni adjustment.

The areas under the glycemic curve (AUC) will be calculated using the trapezoidal method, considering the area above baseline values (Tosh, 2013). The Shapiro-Wilk, Levene and Mauchly tests will be applied to assess whether the data present normal distribution, homoscedasticity and sphericity, respectively. The effect of the tested meals on glycemic AUC or appetite scores will be measured by one-way ANOVA with repeated measures with Bonferroni *post hoc comparisons* .

The tests will be carried out using the SPSS Statistics software version 21.0 (IBM Corporation) with a significance level of 5% being accepted.

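### The 13-session crossover is analysed without a session (period) effect, so any drift common to participants stays in the error and costs precision

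*Protocol*

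**What the plan says.** Section 3.4 lists one standard breakfast and 12 versions with an added food, so a participant who completes the study attends 13 sessions. Their sequence is described only by: "In random order, they will be instructed to consume the standard breakfast, or a standard breakfast plus one of the test foods". The gap between sessions is set by "Washout application will be for a minimum of 3 days and a maximum of 10 days". Among the inclusion criteria in Section 3.2 is "to have availability of time to participate in all meetings within a period of up to 3 months".

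Section 3.5 names two models:

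- For glucose, a two-way repeated-measures ANOVA, introduced with "To examine the effects of the tested meals and time on blood glucose". The time factor is the sampling time from 0 to 120 minutes within one morning, not the session.
- For the area under the curve, a one-way repeated-measures ANOVA on meal, with the area taken above the same morning's baseline.

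Both are followed by Bonferroni comparisons. Session number appears in neither model. The palatability form in Annex II has fields for a randomisation number and a phase, so session appears to be recorded and could be fitted.

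**The concern.** A crossover spread over this many visits should allow for the possibility that participants respond differently late in the series than early. Treatment, diet, season or familiarity with the procedure could change the response over weeks. The protocol states the factors of both models, so the omission is in what it fixes and is not merely a detail left for a later plan.

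If such a change is common to participants and is not modelled, it has two effects. It adds to the within-person residual, which widens every interval. It also lets the chance placement of meals over sessions move the observed differences. The standard breakfast is eaten once per person and is the reference for all 12 foods, so part of that movement is shared by all 12 comparisons. What is at stake is power and the width of intervals in a study of 22 people that also pays for Bonferroni adjustment.

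**Working it through.** **Inputs from the protocol.** 13 meals (Sections 2.2 and 3.4); 22 participants (Section 3.2); washout of 3 to 10 days (Section 3.4); models as in Section 3.5.

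**The plan's own figure.** Section 3.2 takes 19 participants and adds 15%: 19 × 1.15 = 21.85, rounded up to 22. This reproduces. The 19 cannot be reproduced, because no effect size, SD, within-person correlation or power is given. The drift loss therefore cannot be set against a planned power.

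**Length of the series.** 12 gaps × 3 days = 36 days; 12 gaps × 10 days = 120 days. The inclusion criterion sets the upper end at 3 months.

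**Chance imbalance in session position.** This assumes an independent random order for each participant.

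- Variance of one position among 13: (13² − 1)/12 = 14.
- Variance of the difference between two positions in one order: 2 × 14 × 13/12 = 30.3.
- Variance of the mean difference over 22 participants: 30.3/22 = 1.38, so the SD is 1.17 sessions.
- Two food-versus-standard differences share the standard breakfast, so their shifts correlate at 0.5. The average shift over the 12 foods has SD √(14/22) × 13/12 = 0.86 sessions.
- By simulation, the largest of the 12 imbalances against the standard breakfast has a median of 2.0 sessions and a 95th percentile of 3.2.

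**Effect of drift on precision.** Let D be a linear drift common to participants from session 1 to session 13, in within-person residual SDs. The documents give no value, so D is an assumption shown over a range. The drift per session is D/12, and the within-person variance of session number is 14 × 13/12 = 15.17. Error variance is therefore multiplied by 1 + 15.17 × D²/144 = 1 + 0.105 × D².

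| D (assumed) | Error variance multiplied by | 22 participants carry the information of |
|---|---|---|
| 0.5 | 1.03 | 21.4 |
| 1 | 1.11 | 19.9 |
| 2 | 1.42 | 15.5 |
| 3 | 1.95 | 11.3 |

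**Power by simulation.** Each setting used 3,000 trials with 22 participants, 13 meals, independent residuals and one meal differing by an assumed 0.95 residual SD. The entries are for the overall meal test.

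| D | Meal only, as planned | Meal plus categorical session |
|---|---|---|
| 0 | 82% | 80% (79.5%) |
| 1 | 75% | 78% (77.5%) |
| 2 | 62% | 79% |
| 3 | 45% | 77% |

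**Bias and type I error.** In the same simulations without the session term, the mean error of a meal difference was at most 0.015 SD in absolute size for every D. With no true meal effect, the rejection rate was 4.7% to 5.5% without the term and 4.4% to 5.5% with it.

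**Cost in degrees of freedom.** The one-way analysis has 12 × 21 = 252 error degrees of freedom. A 13-level session effect takes 12 and leaves 240.

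**The case against.** The strongest reply is that randomising the order already deals with drift. Chance imbalance is part of the residual, so the standard errors and p-values reflect it. This stands. A reader might infer that the food effects will be biased, or that drift will produce false positives. Neither the design nor the simulations support that. The shared component in the 12 comparisons is also true of any chance error in a shared reference.

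Second, no drift size is documented. A 20% fall in the glycemic area over the series, with a within-person coefficient of variation of 20%, 25% or 30% (all assumed), corresponds to D = 1, 0.8 or 0.67. It would raise the standard error of a contrast by only about 5%, 3% or 2%. This stands too and limits the size of the point.

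Third, the protocol contains measures against drift: the area is taken above the same morning's baseline, the previous evening's meals are standard, fasting time is fixed within limits, and a session is postponed if home glucose is outside 80 to 200 mg/dL. These help only in part. Subtracting baseline removes drift in the fasting level but not in the size of the response, and the time-by-time glucose comparison has no baseline subtraction.

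Two further inferences should be resisted. Section 3.3 says "Volunteers will be instructed to follow individualized nutritional prescriptions", which might be read as a continuing dietary treatment that drives drift. The same sentence gives rules for the 24 hours before a session, so it may be no more than preparation. Likewise, the protocol states no balancing of meals over sessions, but a balanced list may exist in a randomisation plan that is not shown. The missing session term depends on neither inference.

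**Conclusion.** The point holds as one of precision. The two models named in Section 3.5 leave out the period effect of a 13-period crossover, so common drift would inflate the error. The loss is negligible up to about half a residual SD of drift (under 3% of error variance), becomes material from about 1 SD (11%), and is large at 2 to 3 SD (42% to 95%). These figures assume linear drift common to all participants and independent random orders; the drift sizes are assumptions. The meal effects remain unbiased on average and the type I error remains near 5%. The change is worth making because it is cheap and protects power, not because the planned analysis is invalid.

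**What to change.** In Section 3.5, replace the two repeated-measures ANOVAs with linear mixed models, which the same software can fit:

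- Area under the curve: participant random; meal and session number (1 to 13) fixed.
- Glucose curve: the same terms plus minutes and meal by minutes, with a stated covariance for the seven readings of one morning.

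Keep the Bonferroni comparisons. State how the order list is generated. If it is not already balanced over sessions, draw it from a 13 × 13 Latin square or a Williams set; 22 participants allow only approximate balance.

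The cost is 12 of 252 error degrees of freedom, about 3 points of power on the overall meal test if there is no drift, and a rewritten model statement, because classical repeated-measures ANOVA does not readily take a factor whose value for a given meal varies between people. Two limits remain. Drift that differs between participants is not removed, and with gaps of 3 to 10 days session number is only a rough measure of elapsed time.

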**3.5 Statistical Analysis:**

Sample characterization data and meal palatability will be analyzed using the mean ± standard deviation. To compare the average palatability scores, the Shapiro- Wilk test will be applied.

To examine the effects of the tested meals and time on blood glucose, two-way analysis of variance (ANOVA) with repeated measures will be performed with *post hoc* comparisons using the Bonferroni adjustment.

The areas under the glycemic curve (AUC) will be calculated using the trapezoidal method, considering the area above baseline values (Tosh, 2013). The Shapiro-Wilk, Levene and Mauchly tests will be applied to assess whether the data present normal distribution, homoscedasticity and sphericity, respectively. The effect of the tested meals on glycemic AUC or appetite scores will be measured by one-way ANOVA with repeated measures with Bonferroni *post hoc comparisons* .

The tests will be carried out using the SPSS Statistics software version 21.0 (IBM Corporation) with a significance level of 5% being accepted.

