**2.2 Specifics:**

**I)** To measure the glycemic response at times 0/15/30/45/60/90/120 minutes after consumption of the tested meals, which will be:

- Standard breakfast;

- Standard breakfast plus 3 g of cinnamon powder;

- Standard breakfast plus 3 g of cinnamon capsules;

- Standard breakfast plus 6 g of cinnamon powder;

- Standard breakfast plus 6 g of cinnamon capsules;

- Standard breakfast plus 100 g of lettuce;

- Standard breakfast plus 100 g of tomato;

- Standard breakfast plus 30 ml of extra virgin olive oil;

- Standard breakfast plus 115g of mixed salad containing 50 g of lettuce, 50 g of tomato and 15 ml of extra virgin olive oil;

- Standard breakfast plus 150 g of avocado;

- Standard breakfast plus 15 g of wheat bran;

- Standard breakfast plus 15 g of chia seeds and

- Standard breakfast plus 15 g of golden linseed flour;

**II)** – To check the effect of the tested meals on palatability;

**III)** To compare the time-to-time glycemic responses resulting from the evaluated meals and

**IV)** – To analyze the behavior of the curve and the area below the glycemic curve (at times 0/15/30/45/60/90/120 minutes) after consuming tested meals.

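### Section 3.5 assigns a normality test to the comparison of palatability scores, which leaves Objective II without a valid comparative test

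*Protocol*

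**What the plan says.** Objective II in Protocol section 2.2 is "To check the effect of the tested meals on palatability". Section 3.4 has participants complete a visual analogue scale (VAS) after each meal "to assess palatability, considering appearance, smell, texture, flavor and intensity of flavors (sweet, salty, bitter and sour").

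Section 3.5 gives palatability two provisions. The first is descriptive: "meal palatability will be analyzed using the mean ± standard deviation". The second is presented as the comparison: "To compare the average palatability scores, the Shapiro- Wilk test will be applied".

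Later in section 3.5, the same test appears in a different role: "The Shapiro-Wilk, Levene and Mauchly tests will be applied to assess whether the data present normal distribution, homoscedasticity and sphericity, respectively". The within-subject comparison of meals is then set out for other outcomes: "The effect of the tested meals on glycemic AUC or appetite scores will be measured by one-way ANOVA with repeated measures". Its pairwise follow-up is Bonferroni-adjusted. The two-way repeated-measures ANOVA is for blood glucose. The section closes "with a significance level of 5% being accepted".

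**The concern.** Objective II asks whether palatability differs between meals: the standard breakfast and 12 test meals, all eaten by the same participants. That calls for a within-subject comparison of 13 conditions. Shapiro-Wilk addresses another question, namely whether a set of scores could have come from a normal distribution.

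An analyst who followed the sentence literally could err in two ways. Meals that truly differ in mean palatability would not be distinguished by the test. Skewed scores, which are plausible on a bounded scale, could give a small p-value that is taken for a difference between meals. Because the protocol names a test for this comparison and names the wrong one, this is not a detail left to a statistical analysis plan. A plan that copied the sentence would carry the error forward.

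**Working it through.** The protocol gives no figure to reproduce here. The check has two parts: which outcome is matched to which method, and how the named test behaves.

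**Matching outcomes to methods in section 3.5**

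| Outcome | Method named | Compares meals? |
|---|---|---|
| Blood glucose over time | Two-way repeated-measures ANOVA, Bonferroni | Yes |
| Glycemic AUC | One-way repeated-measures ANOVA, Bonferroni | Yes |
| Appetite scores | One-way repeated-measures ANOVA, Bonferroni | Yes |
| Palatability | Mean and SD; Shapiro-Wilk | No |

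Palatability is the only outcome with an objective of its own that receives no method able to compare meals.

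**Why Shapiro-Wilk does not respond to the mean**

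The statistic is W = (Σ aᵢx₍ᵢ₎)² / Σ(xᵢ − x̄)², where the x₍ᵢ₎ are the ordered scores and the weights aᵢ sum to zero. Add a constant c to every score:

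- the numerator sum gains c·Σaᵢ = 0;
- each deviation xᵢ − x̄ is unchanged.

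W and its p-value therefore stay the same whatever c is. This is algebra and needs no assumption about the size of palatability differences. It applies to the scores of one meal and to the paired differences between two meals. If the scores of all meals were pooled, shifts between meals could alter the overall shape, but a rejection could not separate a meal difference from skewness or say which meals differ.

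Numerical confirmation: one simulated normal sample of n = 22 gave W = 0.9676 and p = 0.6545. After 30 was added to every score, W = 0.9676 and p = 0.6545.

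**Illustration against the ANOVA already in the protocol**

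From the protocol: 22 participants, 13 meals, 5% level. Assumed, because the protocol gives no VAS variability: mean 50, between-subject SD 10, within-subject SD 15, and one meal shifted by 0, 10 or 20 points. Shapiro-Wilk is applied to the shifted meal's scores. There were 4,000 runs per row.

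| True shift of one meal | Shapiro-Wilk rejects | Repeated-measures ANOVA rejects |
|---|---|---|
| 0 | 5.5% | 4.7% |
| 10 | 5.9% | 44.8% |
| 20 | 5.0% | 99.2% |

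In a fourth setting, scores were skewed (exponential, SD 15, no between-subject component) and all meal means were equal. Shapiro-Wilk rejected in 88.5% of runs and ANOVA in 4.9%.

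The ANOVA percentages depend on the assumed SDs. The flat Shapiro-Wilk column does not: for normal scores it stays near 5% at any SD and any shift.

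**The case against.** The strongest reply is that this is a slip of drafting or translation. Section 3.5 describes Shapiro-Wilk correctly later on, so the authors know what it does. The sentence may have lost a clause saying that normality would be checked before a comparison. That is likely, and it makes a false report of a palatability difference improbable in practice. It does not repair the text, because palatability has its own sentence and no other sentence supplies the missing comparison.

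A second reply is that the appetite scores in the ANOVA sentence were meant to include palatability. The text does not say so: section 3.4 describes palatability through sensory attributes, and appetite is a different construct.

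A third reply is that real differences would not be hidden, since means and standard deviations are to be reported by meal. This is correct. A large difference would be visible, but untested.

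A reader might infer more than the protocol supports on two points. The first is that appetite is an outcome with no instrument behind it, so that the term should be struck out or replaced by palatability. The Annex II form carries hunger and fullness anchors (left in Portuguese), and the reference cited for the VAS is, by its title, a methods study of appetite sensations after single test meals. Appetite data may well be collected, and removing the term would leave those items without an analysis. What does stand is narrower: no objective lists appetite, and section 3.4 presents the VAS as a palatability scale only. The second is that the error reaches the trial's glycemic results. It does not, because those outcomes have their own methods.

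**Conclusion.** The point holds. As written, Objective II has a descriptive summary and no valid comparative test. The test named for the comparison cannot respond to a difference in means, and this follows from its definition, not from any assumed variability.

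Severity is moderate. The protocol does not rank its objectives, but the general objective and specific objectives I, III and IV all concern glycemia, and palatability is the remaining one of four. The glucose ANOVA, the AUC analysis and the sample size are unaffected. The conclusion rests only on the wording of sections 2.2, 3.4 and 3.5. The simulated rejection rates are illustrative and carry no weight in the grading.

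**What to change.** Make three edits to the protocol text.

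1. In section 3.5, delete the sentence that uses Shapiro-Wilk to compare palatability. Keep Shapiro-Wilk where it appears with Levene and Mauchly, as an assumption check.
2. Extend the existing one-way repeated-measures ANOVA sentence to three outcomes: glycemic AUC, each palatability VAS item, and appetite scores. Keep the Bonferroni post hoc comparisons. Add that, if the data are clearly non-normal, Friedman's test with Bonferroni-adjusted pairwise comparisons will be used.
3. State whether appetite is an outcome. If it is, describe its measurement in section 3.4 and add it to the objectives. If it is not, say what the hunger and fullness items in Annex II are for. In either case, reconcile section 3.4 with the form.

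The Bonferroni adjustment should stay even if the comparisons are limited to each of the 12 test meals against the standard breakfast. Twelve unadjusted tests at 5% would give a familywise error of 1 − 0.95¹² = 0.46 per item if they were independent, and somewhat less with the shared control.

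The cost is wording only. The VAS is already scheduled after every meal, so no visit, measurement or participant is added.

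### The meal-by-time ANOVA leaves each visit's pre-meal glucose unadjusted and counts it as an outcome, which costs precision in the meal main effect and the per-time comparisons

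*Protocol*

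**What the plan says.** Protocol section 3.5 fixes the time-point model: "To examine the effects of the tested meals and time on blood glucose, two-way analysis of variance (ANOVA) with repeated measures will be performed", with Bonferroni post hoc comparisons. The outcome is blood glucose. No covariate or change from baseline is mentioned, and the levels of the time factor are not listed there.

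The times are given elsewhere. Section 3.4: "The glycemic curve will be monitored for 120 minutes at times 0, 15, 30, 45, 60, 90 and 120 minutes". Section 2.2, Objective I: "To measure the glycemic response at times 0/15/30/45/60/90/120 minutes after consumption of the tested meals". Objective III, which this model serves, is "To compare the time-to-time glycemic responses resulting from the evaluated meals".

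The AUC is handled differently within section 3.5. It is calculated "considering the area above baseline values", and then: "The effect of the tested meals on glycemic AUC or appetite scores will be measured by one-way ANOVA with repeated measures". Neither analysis is named as primary.

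On the test days, section 3.4 sets a random meal order, a washout of 3 to 10 days, and an entry rule on a home reading: if it "is lower than 80 mg/dL or higher than 200 mg/dL, they will not participate in the intervention on that day".

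**The concern.** The 13 meals are eaten on 13 separate days, and the same person will not start each day at the same fasting level. A higher start tends to lift the whole curve. A model of unadjusted glucose puts that lift into the difference between two meals, whether averaged over time or taken at one time point. The AUC analysis removes it by subtraction; the time-point analysis does not.

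There is a second, smaller effect. If time 0 is taken before eating, no meal can influence it, yet it is averaged into the meal main effect with the same weight as the six later readings.

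With 22 participants and a Bonferroni correction over many meal pairs, avoidable noise could hide a real food effect in the analysis meant to answer Objective III.

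**Working it through.** **Inputs from the protocol.** 22 participants; 13 meals (standard plus 12 foods); 7 times including 0; 5% level; Bonferroni. All pairs of 13 meals: 13 × 12 / 2 = 78, so 0.05 / 78 = 0.00064 per pair.

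**The plan's own figure.** Section 3.2 takes 19 and adds 15%: 19 × 1.15 = 21.85, rounded to 22. This reproduces. The base of 19 cannot be rebuilt, because effect size, SD and power are not given. No within-person SD or correlation of glucose is given either, so those below are assumptions.

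**Step 1: where a fasting shift goes.** Suppose a visit starts s mg/dL higher and the whole curve moves by s.
- Meal difference at one time, unadjusted: contains s in full.
- Meal main effect (mean over times): contains s in full.
- Meal-by-time interaction (change within a visit): s cancels.
- AUC above baseline: s cancels.

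**Step 2: dilution.** With mean post-meal effect d and zero expected effect at time 0, the average over seven times is (0 + 6d) / 7 = 0.857d. For d = -15 mg/dL this is -12.9. Comparisons at 15 to 120 minutes are not diluted.

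**Step 3: precision.** With r the within-participant, between-day correlation of time-0 and later glucose, adjustment multiplies contrast variance by about 1 - r². The equivalent unadjusted sample is 22 / (1 - r²). Subtracting baseline instead gives 2(1 - r), if the variances at the two times are equal.

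| r (assumed) | Variance, adjusted | Equivalent n | Variance, change score |
|---|---|---|---|
| 0 | 1.00 | 22 | 2.0 |
| 0.3 | 0.91 | 24 | 1.4 |
| 0.5 | 0.75 | 29 | 1.0 |
| 0.7 | 0.51 | 43 | 0.6 |
| 0.8 | 0.36 | 61 | 0.4 |

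**Step 4: simulation.** 1,500 trials per setting (22 × 13 × 7). Assumed: effect of -15 mg/dL at all six post-meal times for one meal, independent residual SD 10, between-participant SD 25, two-sided test at 0.00064. The entries are the power of one meal against standard for a time-averaged contrast. The last two columns subtract baseline.

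| Between-day fasting SD; share carried through the curve | 7-time mean | 6-time mean, unadjusted | 6-time mean, adjusted | 6-time mean minus time 0 | AUC above baseline |
|---|---|---|---|---|---|
| 5; full | 1.00 | 1.00 | 1.00 | 0.88 | 0.84 |
| 10; full | 0.70 | 0.88 | 1.00 | 0.86 | 0.82 |
| 15; full | 0.25 | 0.40 | 0.98 | 0.89 | 0.84 |
| 20; full | 0.09 | 0.15 | 0.94 | 0.86 | 0.82 |
| 15; half | 0.86 | 0.99 | 1.00 | 0.60 | 0.53 |
| 15; none | 1.00 | 1.00 | 1.00 | 0.22 | 0.17 |

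The simulated 7-time effect was -12.8 to -13.0, as Step 2 predicts. At SD 15 with full carry-through, the standard deviation of the estimate is 4.68 for seven times and 4.72 for six. Including time 0 therefore cuts the effect by 14% and the noise by about 1%.

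**Step 5: a single time point gains less than the mean.** In the same set-up at SD 15, one time point has r = 225 / (225 + 100) = 0.69, so the variance factor is 0.52. For the six-time mean, r² = 225² / (325 × 241.7) = 0.64, so the factor is 0.36. The power table therefore overstates what each per-time comparison would gain.

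**The case against.** The strongest reply is that two planned routes to a meal effect already remove the fasting level: the meal-by-time interaction and the AUC above baseline. This stands. A reader might infer that every meal contrast is contaminated, or that the meal effect is diluted throughout; section 3.5 supports neither.

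A reader might also take 80 to 200 mg/dL as the spread of one person's starting values. It is an entry window on a home reading, applied to all participants, and says nothing about within-person variation. The protocol also restrains that variation with standard meals the evening before, an 8 to 11 hour fast, a fixed arrival window, and no alcohol or exercise for 24 hours. The fasting SD may be modest, and the gain with it.

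Nor is there systematic bias. Meal order is random, so fasting differences are chance variation already in the error term, and the test keeps its level.

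The premise is also partly inferred. Section 3.5 does not list the time levels, and Objective I places time 0 among times after consumption. Against that, an area above baseline needs a baseline, and time 0 is the only scheduled curve reading that can serve.

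Finally, covariates can be left to a statistical analysis plan, which is not at hand. But the protocol does not leave the model open: it names one, without adjustment.

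What remains is a loss of precision in two places, the main effect and the per-time comparisons. The second is what Objective III asks for.

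**Conclusion.** The point holds as a free improvement in precision. On the natural reading of sections 2.2, 3.4 and 3.5, unadjusted glucose is modelled with a pre-meal value as one of seven levels.

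- **Certain, given that reading:** the time-averaged meal main effect is 6/7 of the mean post-meal effect.
- **Dependent on r, which the protocol does not give:** the variance that adjustment would save, from nothing at r = 0 through 25% at r = 0.5 to 64% at r = 0.8.

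Where no fasting shift carries through, the simulated adjusted and unadjusted six-time means perform alike (power 1.00, standard deviation of the estimate 1.23 for both), so the change has essentially no downside. The documents do not support calling the planned analysis biased or invalid. All of this rests on time 0 being taken before eating. If it were taken after the meal, it could carry a meal effect and would be unsuitable as a covariate.

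**What to change.** 1. In section 3.4, state that time 0 is measured before the first bite, and bring the wording of Objective I into line.
2. In section 3.5, take the 15 to 120 minute values as the outcome, with meal, time, meal-by-time and participant effects, and same-visit time-0 glucose as covariate. Keep the correlation of readings within a visit in the model. Use fixed participant effects, or add each participant's mean time-0 value, so that the slope reflects day-to-day differences within a person.
3. Make no meal comparisons at time 0.

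Prefer the covariate to a change score: subtraction adds variance when r is below 0.5 (Step 3).

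Cost: one degree of freedom and revised wording. No extra measurement, visit or participant is needed. Because the covariate changes from visit to visit, the model is most simply fitted as a linear mixed model.
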